**Figure 3 F3:**
[figure not shown]
Trial profile.

#### Study settings

A convenience sample will be recruited in Jiangsu and Qingdao, China, via two local MSM-related CBOs. The two CBOs are run by non-medical community staff trained to perform rapid HIV testing and consultation, PEP and PrEP counseling, and psychological support for HIV-negative and positive clients. Both CBOs have rich experience in HIV research and management. Offline PEP prescription will be conducted at Suzhou Fifth People's Hospital (Jiangsu) and Qingdao Sixth People's Hospital (Qingdao, China), both of which are among the designated PEP treatment hospitals under the national PEP uptake guideline (32).

#### Randomization

Simple randomization, stratified by baseline HIV risk assessment (low risk vs. high risk) will be performed once the baseline survey and HIV risk assessment are finished. An HIV infection risk assessment tool specifically designed for Chinese MSM was used in our study for HIV risk assessment (33). Variables included in the tool were the number of homosexual partners, HIV-positive homosexual partners, commercial male sexual behaviors, unprotected anal intercourse with men, diagnosis of sexually transmitted diseases, sex role during anal sex with a man, recreational drug usage, and group sex with men. All variables were reported for the previous 6 months. The total score in the tool ranges from 0 to 15, with scores of 5 and above being at high risk of HIV infection. The HIV infection risk assessment tool has been externally validated in different Chinses MSM groups and showed good discrimination performance for HIV infection risk (34, 35). Participants are finally assigned to the O2O-PEP or the control group in a 1:1 ratio with a computerized randomization algorithm by SAS 9.4. The computer-generated sequence will be generated by an independent statistician who is not involved in this study. After randomization, the participant will be automatically guided to the web link associated with their allocation. Study researchers and participants are both blinded to the allocation sequence.

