#### Procedures

##### Participant enrollment

To recruit participants, we will post a clickable study advertisement through the official online WeChat accounts of the two local CBOs. The advertisement includes a brief introduction about the study and a QR code, which can be scanned by the participant for study entry. Interested MSM who scan the QR code will be directed to a simplified Chinese web-based eligibility screener at the “Wen Juan Xing” web portal to determine their age, gender, sexual behaviors, HIV status, state of residence, and availability of Android operation system-based smartphone, and then directed to the electronic consent form, the baseline survey, and HIV risk assessment. All participants who meet eligibility criteria and complete the baseline survey and risk assessment will be assigned to two groups based on stratified randomization; the O2O-PEP group and the control group. In addition, participants will also be recruited in communities by the two CBO working staff who will proactively introduce this study to potential participants.

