##### Sample size

Our previous study found that ~5% of MSM self-reported using PEP before the survey (36). A sample of ~400 participants (200 per group) would achieve 90% power to detect a moderate effect corresponding to a difference of at least 9% points (equivalent to a relative risk of 2.8 assuming a 5% prevalence of PEP usage in the control group) in PEP uptake between the intervention and control groups using a two-sided test at a 5% significance level and assuming a 10% attribution rate after 6 months. According to Cocks et al. (37) the sample size of a pilot trial should be at least 9% of that of the main planned trial. Hence, we plan to recruit 50 participants, 25 per group, to assess preliminary evidence for the further main study.

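### Simple randomization within HIV-risk strata is equivalent to no stratification, so the pilot enforces neither risk balance nor arms near 25 each

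*Protocol article*

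**What the plan says.** The Randomization section of the protocol article names the method: "Simple randomization, stratified by baseline HIV risk assessment (low risk vs. high risk) will be performed". The strata come from a 0-to-15 risk score, "with scores of 5 and above being at high risk of HIV infection". Participants are "assigned to the O2O-PEP or the control group in a 1:1 ratio", from a sequence that an independent statistician generates in SAS. No blocking, minimization or other restriction is named.

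The Participant enrollment section says that eligible men "will be assigned to two groups based on stratified randomization; the O2O-PEP group and the control group". The Abstract, the Study design and participants section and the Discussion also describe a stratified trial. The Sample size section gives the target: "we plan to recruit 50 participants, 25 per group". The Statistical analysis plan section evaluates PEP initiation with an unadjusted risk ratio.

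**The concern.** Stratifying has an effect only if allocation is restricted within each stratum, for example by permuted blocks. Simple randomization is the standard term for unrestricted allocation, in which each participant is assigned independently. The two halves of the sentence therefore cancel. If simple is meant, the word stratified does no work; if real stratification is meant, the word simple is wrong. This is a method stated wrongly, not a block size left to a fuller document.

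The investigators chose HIV risk as the factor to control. The score counts, among other things, unprotected anal intercourse, HIV-positive partners and group sex, which plausibly govern who has an exposure that warrants PEP. At stake is chance imbalance on that factor in a 50-person trial whose efficacy analysis does not adjust for it.

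**Working it through.** **Inputs from the article.** Total 50, target 25 per arm, allocation 1:1, two risk strata; assumed PEP uptake of 5% in controls and, with a difference of 9 points, 14% under the intervention (Sample size section, main-trial assumptions).

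**Input not in the article.** The number of high-risk men. A range of 10 to 25 out of 50 (20% to 50%) is assumed.

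The pilot size of 50 has no formula to reproduce. Its stated basis is a floor of 9% of the main trial, 0.09 × 400 = 36, which 50 meets.

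**1. Equivalence.** Under simple allocation each participant is assigned with probability 0.5, independently of all others. Splitting the participants into strata first does not change that joint distribution. Simulation (15,000 trials per setting) agrees. The standard deviation (SD) of the between-arm difference in high-risk share was:

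| High-risk men | Simple within strata | Simple, no strata | Permuted blocks of 4 within strata |
|---|---|---|---|
| 10 | 0.114 | 0.116 | 0.037 |
| 15 | 0.133 | 0.133 | 0.030 |
| 20 | 0.142 | 0.142 | 0.019 |
| 25 | 0.144 | 0.145 | 0.028 |

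**2. Arm sizes.** One arm's size follows Binomial(50, 0.5), with SD √50/2 = 3.5.
- P(exactly 25:25) = C(50,25)/2^50 = 11.2%
- P(28:22 or worse) = 48.0%
- P(30:20 or worse) = 20.3%

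**3. Balance on risk.** With 15 high-risk men, P(10:5 or worse in that stratum) = 2 × P(Binomial(15, 0.5) ≥ 10) = 30.2%. Enumerating all splits of both strata, P(arms differ by at least 15 points in high-risk share) is 19%, 26%, 28% and 32% for 10, 15, 20 and 25 high-risk men.

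**4. What an imbalance could do to the risk ratio.** Expected PEP initiations are 25 × 0.05 = 1.25 and 25 × 0.14 = 3.5. Take the extreme case in which all uptake comes from high-risk men and the intervention does nothing. A 10:5 split with 25 per arm gives high-risk shares of 10/25 = 40% and 5/25 = 20%, so imbalance alone gives a risk ratio of 40/20 = 2.0. A 15-point gap of 37.5% versus 22.5% gives 37.5/22.5 = 1.67. The effect size in the Sample size section is 2.8.

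**5. Sampling error, for comparison.** SE(log RR) = √(1/1.25 − 1/25 + 1/3.5 − 1/25) = 1.00. The 95% interval therefore runs a factor of exp(1.96 × 1.00), about 7, in each direction.

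**6. Under restriction.** With blocks of at most 4 within each stratum, the arms differ by at most 2 per stratum. If both strata are off by 2 in the same direction the total gap is 4, which is a 27:23 split. The high-risk share then differs by at most 8 points for the stratum sizes above. Exactly 25:25 is still not assured: with blocks of 4 it occurred in about 50% to 67% of simulated trials.

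**The case against.** The strongest reply is that little harm follows. Simple randomization is valid: the comparison is unbiased and balance holds in expectation. Unequal arms cost little, since a 30:20 split keeps 4 × 0.6 × 0.4 = 96% of the efficiency. The trial is a pilot. Two of its three primary outcomes (the usability score and mini-app exposure time) concern an app that controls do not receive, so risk balance between arms does not bear on them. The Discussion already concedes the small sample. All of this stands, and it limits the severity.

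A reader might infer that a chance risk imbalance could create or hide the whole treatment effect. The figures do not support that. Even if all uptake came from high-risk men, a 10:5 split of 15 such men yields a risk ratio of about 2.0 against the planned 2.8, and ordinary sampling error is much larger. A reader might also infer that the design cannot be repaired once enrolment starts. It can: the remaining sequence can be amended and the recorded risk stratum used in the analysis. Nor is the figure of 25 per group a promise of the realised split, and blocking would not guarantee it.

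Finally, simple may be loose wording for a restricted scheme, given the repeated references to stratification. That is possible, but the text does not say so, and the sentence needs correcting on either reading.

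**Conclusion.** The point holds as a should-fix. As written, the stratification has no effect on balance. The probabilities for arm size (11% for 25:25, 20% for 30:20 or worse) are exact and rest only on 1:1 simple allocation of 50. The 19% to 32% chance of a gap of 15 points or more rests on the assumed 10 to 25 high-risk men; the equivalence itself needs no such assumption. The consequence is avoidable noise on the prognostic factor the investigators selected, carried into an unadjusted risk ratio with very few events. It is neither bias nor a threat to the validity of the comparison.

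**What to change.** In the Randomization section, replace the words simple randomization, stratified with: *permuted-block randomization with concealed, randomly varying block sizes within each risk stratum, 1:1*. The independent statistician should hold the block sizes, and they should not appear anywhere that recruiting community-organization staff can read them, because those staff approach participants directly and an assignment becomes visible once made.

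The cost is one sentence and a regenerated SAS sequence; the independent statistician and the automated assignment are already in place. The downside is slight predictability of assignments, which concealed and varying block sizes keep small.

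This is best done before the first assignment. If enrolment has begun, change the remaining sequence by amendment and report a risk ratio adjusted for risk stratum, for example by Mantel-Haenszel.

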#### Step 1. Establishing an integrated interdisciplinary team

Our interdisciplinary team consists of an online service team, an offline service team, and a technology team. The online service team includes HIV researchers and community-based organization (CBO) working staff, whose main task is to develop online PEP healthcare education packages and provide e-counseling support when needed. A doctor and a nurse in a hospital specializing in HIV management compose the offline service team, whose main task is to start a PEP regimen (the doctor) and PEP counseling for MSM (the nurse). The O2O-PEP model will be developed with VeiRui Technology (Beijing, China), a firm specializing in developing gamification-based software. The authors ([name], [name], and [name]) will be directly involved in creating requirements for the model.

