**Laboratory testing**					
HIV Ag/Ab testing	HIV-1/2	√	√	√	√
Syphilis	Syphilis serology	√	√		√
Gonorrhea/ Chlamydia	first-catch urine, oral, urethral, and rectal mucosal secretions	√	√		
HBV	HBsAg, anti-HBs, anti-HBc	√			√
HCV	HCV antibody test	√			√
Serum creatinine	Kidney function test	√	√		
ALT, AST	Liver function test	√	√		

The primary efficacy outcome is PEP initiation. PEP initiation data will be collected through the clinical records in the study hospitals, which is a binary variable (1 = PEP initiation during the study period, otherwise 0). The acceptability outcome will be measured by the System Usability Scale (SUS) (30). For feasibility, we will assess the cumulative exposure time to the mini-app, as well as time spent on specific components of the mini-app, which will be automatically collected by participant application log files.

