##### Statistical analysis plan

All statistical analyses will be conducted using SAS software (version 9.4, SAS Institute, Inc. USA), with a two-sided *p*-value of <0.05 considered statistically significant. The primary analysis will be performed by intention-to-treat analysis. Descriptive statistical analysis will be first carried out to report baseline demographics, outcome variables, and other covariates at different follow-up time points, and then compared with Chi-square/Fisher exact probability tests (for categorical variables) or *t*-test/Mann Whitney U test (for continuous variables) between those who finish follow-ups and those who do not and between the mini-app group and the control group.

The preliminary efficacy of the min-app intervention to increase PEP initiation (any PEP initiation over follow-ups) will be evaluated using an unadjusted risk ratio. As for model acceptability, point estimates for a SUS score of ≥50 will be considered the minimum criteria for acceptability. Descriptive analysis will be used to evaluate model usability, including cumulative time to the mini-app, and time spent on specific components of the mini-app. Multiple imputations will replace missing data, and a sensitivity analysis will be performed to compare the multiple imputation analysis with the full case analysis.

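### Site is left out of both the randomization and the unadjusted comparison, so a chance site imbalance passes into the PEP-initiation estimate: a small effect, cheaply avoided

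*Protocol article*

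**What the plan says.** Under Study settings the protocol describes two recruiting areas: "A convenience sample will be recruited in Jiangsu and Qingdao, China, via two local MSM-related CBOs". Each area has its own prescribing hospital: "Offline PEP prescription will be conducted at Suzhou Fifth People's Hospital (Jiangsu) and Qingdao Sixth People's Hospital".

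Under Randomization, the method is simple randomization, and its only stratification factor is given with it: "stratified by baseline HIV risk assessment (low risk vs. high risk"). The ratio follows: "Participants are finally assigned to the O2O-PEP or the control group in a 1:1 ratio". Site is not named as a factor.

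Under Outcomes and covariates of the study, the primary efficacy outcome is tied to the two hospitals: "PEP initiation data will be collected through the clinical records in the study hospitals". It is binary. Site is not in the covariate list of Table 1 or in the text that explains it.

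Under Statistical analysis plan, the efficacy comparison "will be evaluated using an unadjusted risk ratio".

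**The concern.** The outcome is an act carried out, and recorded, at a particular hospital, so site is an obvious candidate predictor in both arms. PEP has to begin within 72 hours of exposure, and the two catchments differ: the eligibility criteria admit residents of a whole province on one side and of a single city on the other. Travel distance, clinic access and local practice could each make a start more likely at one hospital than at the other.

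If one arm happens to contain more men from the site with higher uptake, part of the observed difference in PEP starts belongs to the hospital and not to the mini-app. Nothing in the allocation limits this, and nothing in the stated comparison removes it. At stake is how readable the preliminary efficacy estimate is, because it is meant to inform a main trial of about 400 men.

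**Working it through.** **Inputs from the protocol.** Pilot size 50, 25 per group; control uptake 5%; planning difference 9 points, so 14% under the intervention (all Sample size). Simple 1:1 allocation stratified by HIV risk only (Randomization). Unadjusted risk ratio (Statistical analysis plan). The protocol states no figure for site imbalance, so there is none to reproduce.

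**Inputs assumed, because the protocol does not give them.** Men per site: 25/25, 30/20 or 35/15. Gap in uptake between hospitals: 5 to 10 points, taken as the same in both arms.

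**Step 1: how often is site imbalanced?** Simple randomization within HIV-risk strata is still an independent 1:1 draw for each man, so the strata do not restrain site. Let D be the share of men from site A in the intervention arm minus that share in the control arm. Two readings were calculated: independent allocation as written, and arm totals held at 25/25 (hypergeometric) with site ignored.

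| Men per site | P(\|D\| ≥ 20 points), independent allocation | P(\|D\| ≥ 20 points), arms fixed at 25/25 |
|---|---|---|
| 25/25 | 0.20 | 0.26 |
| 30/20 | 0.16 | 0.15 |
| 35/15 | 0.14 | 0.22 |

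The last column is not monotone because the counts are discrete. With arms of 25 and a 30/20 split, the smallest attainable |D| at or above 20 points is 24 points; for the other two splits it is exactly 20. The overall range is about 14% to 26%.

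**Step 2: how far does this move the estimate?** Shift in the risk difference = D × (uptake at site A − uptake at site B).

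- 5-point gap: 0.20 × 0.05 = 0.01, or 1 point.
- 10-point gap: 0.20 × 0.10 = 0.02, or 2 points.

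On the risk-ratio scale, take 15 of 25 men from site A in one arm and 10 of 25 in the other (D = 20 points), with no treatment effect:

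- Uptake 8% and 2%: arm risks (15 × 0.08 + 10 × 0.02)/25 = 5.6% and (10 × 0.08 + 15 × 0.02)/25 = 4.4%; ratio 1.27.
- Uptake 10% and 2%: arm risks 6.8% and 5.2%; ratio 1.31.

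**Step 3: compare with sampling error.** Standard error of the risk difference at 25 per arm:

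- 5% in both arms: √(2 × 0.05 × 0.95/25) = 0.062.
- 5% against 14%: √((0.05 × 0.95 + 0.14 × 0.86)/25) = 0.082.

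A 2-point shift is 0.02/0.062 = 0.32 to 0.02/0.082 = 0.24 of one standard error; a 1-point shift is half that. One PEP start in an arm of 25 is 4 points, so 2 points is half of one man. Controls are expected to have 25 × 0.05 = 1.25 starts, with a probability of 0.95^25 = 0.28 of none at all.

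**Step 4: what would balancing site gain?** In 400,000 simulated allocations with 25 men per site and no treatment effect, the SD of the risk difference fell from 6.2 to 6.1 points for site rates 8%/2%, and from 6.8 to 6.6 points for 10%/2%. The mean risk difference was zero to within simulation error. The type I error of an unadjusted test stayed between 2.1% and 4.9% in every scenario with a site gap (6 to 15 points).

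**Step 5: how large can the gap be?** At 5% control uptake and equal sites, a 10-point gap among controls already needs 10% at one hospital and 0% at the other. A 20-point gap needs a control average of at least 0.5 × 20% = 10% at 25/25, 8% at 30/20 and 6% at 35/15, all above 5%. For these splits it contradicts the protocol's own assumption.

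**The case against.** The strongest reply is that the effect is lost in the noise. The shift is at most about a third of one standard error, it arises at that size in roughly one allocation in four to seven, and balancing site hardly reduces the variance. That stands, and it sets the severity.

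The second reply is purpose. The pilot is for feasibility, acceptability and preliminary evidence, and the Discussion acknowledges the small sample. Leaving a plausible factor unstratified in such a trial is defensible. The documents also point towards similar hospitals: both are designated for PEP and both follow the same national guideline. This too stands as a reason for low severity. It does not show that site is irrelevant, since access and distance can differ under a common guideline.

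Third, counts or estimates by site are commonly left to a statistical analysis plan, and that plan is not shown. Their absence is therefore no fault. The stratification factor and the primary estimator are different, because the article states both and both omit site.

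Fourth, adding site as a factor while keeping simple randomization would balance nothing. This is correct and shapes the fix.

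A reader might also infer more than the text supports:

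- That the comparison is biased or its test invalid. It is not: the shift averages to zero over allocations and the type I error is not inflated.
- That each site has its own doctor-nurse team. The protocol says only: "A doctor and a nurse in a hospital specializing in HIV management compose the offline service team". A team per hospital is an inference, and the point does not need it; two recruiting organizations and two hospitals are explicit.
- That a hospital gap of 20 points could move the result by 4 points. Step 5 shows that such a gap cannot occur among controls at the planned 5% uptake for the site splits considered.

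**Conclusion.** The omission is real, and the protocol text alone establishes it: two recruiting organizations and two hospitals, an outcome read from those hospitals' records, and site in neither the allocation nor the comparison. Its consequence is minor: an occasional, non-systematic shift well inside the pilot's own sampling error. The frequency rests on the assumed site splits, and the size of the shift rests on the assumed uptake gap, applied equally in both arms. The documents give neither figure. The case for acting is the low cost, and the chance that the randomization scheme is carried forward to the main trial.

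**What to change.** In the Randomization section, replace simple randomization with small permuted blocks within site (Jiangsu or Qingdao) by HIV risk (low or high). This makes 2 × 2 = 4 lists, produced by the same SAS program. The gain depends on the blocks: naming site as a further factor under simple randomization would change nothing. The allocation system can read site from the residence item in the web screener, which is completed before randomization. In the report, show PEP-initiation counts by site and arm beside the pooled risk ratio.

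The cost is a change of randomization method in the protocol and two more lists than HIV risk alone requires. No extra participants or new data items are needed. The downside is four strata averaging 50/4 = 12.5 men, probably uneven because neither the site split nor the risk split is known. Some strata will end in an incomplete block, so blocks must be small and balance will be approximate.

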#### Procedures

##### Participant enrollment

To recruit participants, we will post a clickable study advertisement through the official online WeChat accounts of the two local CBOs. The advertisement includes a brief introduction about the study and a QR code, which can be scanned by the participant for study entry. Interested MSM who scan the QR code will be directed to a simplified Chinese web-based eligibility screener at the “Wen Juan Xing” web portal to determine their age, gender, sexual behaviors, HIV status, state of residence, and availability of Android operation system-based smartphone, and then directed to the electronic consent form, the baseline survey, and HIV risk assessment. All participants who meet eligibility criteria and complete the baseline survey and risk assessment will be assigned to two groups based on stratified randomization; the O2O-PEP group and the control group. In addition, participants will also be recruited in communities by the two CBO working staff who will proactively introduce this study to potential participants.

